# The effects of telerehabilitation in adults with complex biventricular congenital heart conditions: protocol for a multi-centre, randomised controlled trial—CH-FIT

**DOI:** 10.1186/s13063-024-08019-7

**Published:** 2024-04-05

**Keywords:** Complex congenital heart anomalies, Combined exercise, Aerobic fitness, Telehealth, Neurocognitive function

## Abstract

**Background:**

Accumulated evidence suggests that exercise training exerts beneficial effects on people with congenital heart conditions. These findings are predominantly derived from small, single-centre exercise trials conducted in outpatient rehabilitation facilities. In recent years, the delivery of exercise interventions remotely has increased through digital communications technology (telerehabilitation). However, very little research to date has been conducted into the efficacy of telerehabilitation in people with a congenital heart condition.

**Aims:**

To evaluate the effects of a telehealth-delivered exercise intervention in people with a history of a surgical biventricular repair due to a congenital heart condition.

**Methods:**

One hundred eligible adolescent (≥ 16 years) and adult participants living with a complex biventricular congenital heart condition will be recruited from four Australian sites and randomised to either (1) a 16-week telehealth-delivered combined (aerobic and resistance) exercise training programme of moderate-to-vigorous intensity or (2) usual care (control group), in a 1:1 allocation, with an 8-month follow-up.

**Outcomes of interest:**

The primary outcome will be the change in aerobic capacity expressed as peak oxygen uptake (VO_2peak_). Secondary outcomes will include changes in vascular function, muscle oxygenation, metabolic profile, body composition and musculoskeletal fitness, neurohormonal activation, neurocognitive function, physical activity levels, dietary and nutritional status, and quality of life. Outcomes will be assessed at baseline, 16 weeks, and 12 months (to determine longer-term maintenance potential).

**Discussion:**

If found to be efficacious, telerehabilitation may be an alternative option for delivering exercise, improving health outcomes, and increasing accessibility to exercise programmes. Efficacy data is required to quantify the clinical significance of this delivery mode of exercise.

**Trial registration:**

ACTRN12622000050752

Trial registration date: 17 January 2022

Trial registration URL: https://www.anzctr.org.au/Trial/Registration/TrialReview.aspx?id=382635&showOriginal=true&isReview=true

Trial registry name: Australian and New Zealand Clinical Trials Registry

**Supplementary Information:**

The online version contains supplementary material available at 10.1186/s13063-024-08019-7.

## Introduction

Congenital heart conditions comprise any abnormality of the heart and central blood vessels present at birth. Elevated rates of morbidity and mortality, high medical resource consumption, and a dearth of efficacious treatments are associated with congenital heart physiologies of varying complexity [1].

Physical activity (PA) and structured exercise in sufficient amounts are recommended preventative and treatment methods for cardiovascular disease (CVD) [2, 3]. Historically, populations with congenital heart conditions have performed PA and exercise at volumes lower than recommended to achieve health benefits [4]. Adults with congenital heart pathologies of varying complexity exhibit impaired aerobic capacity (expressed as peak oxygen consumption; VO_2peak_) relative to age-predicted values, similar to that observed in patients with chronic heart failure [5]. This likely reflects a combination of pathophysiology and deconditioning exhibited by an abnormal ventilatory response to exercise and/or reduced exercise capacity, characteristics found to be associated with an increased 4-year risk of death or cardiac-related emergency hospital admission relative to patients with normal ventilatory responses and higher VO_2peak_ [6], and highlighting the prognostic significance of aerobic capacity. Moreover, an increase in VO_2peak_ of 6% is associated with a reduced mortality risk of 5% in chronic heart failure adults [7]. Although an association between improved aerobic capacity and clinical outcomes has yet to be established for congenital heart adults with varying pathologies, such an association is conceivable given (a) similarities in the pathophysiology between the two conditions and (b) that heart failure in cohorts with congenital heart conditions is the predominant cause of mortality and morbidity compared with chronic heart failure cohorts [8, 9] with > 90% of sudden cardiovascular deaths in adults with congenital heart conditions occurring at rest [10].

Behavioural, physical, and psychological factors contributing to decreased exercise and PA participation and capacity in congenital heart populations are manifold, including advice to avoid exercise [11, 12], reduced confidence to exercise [13], poor self-perception of exercise capacity [14], as well as low lean tissue/adiposity ratio [15], impaired muscle oxidative capacity and strength [16], impaired ventilatory and cardiopulmonary responses to exercise [17, 18], and decreased neurocognitive function [19–22]. However, the risk of adverse events during exercise is very low in people with congenital heart conditions. A recent systematic review reported no progression of symptoms, heart failure, or death, among the 403 participants reviewed [23].

Preliminary findings suggest that adults with congenital heart conditions tolerate and obtain benefit from appropriately prescribed exercise in gym-based programmes [24, 25], including improvement in aerobic exercise capacity and cardiac output [26–28], muscular function [29], and quality of life [30]. However, these studies have been limited by short duration (~ 12 weeks), design (non-randomised), and small sample size (< 50 participants).

To date, there are no randomised controlled trials testing the physiological and neurocognitive response to telerehabilitation treatment in adults with varying biventricular pathologies. Home-based cardiac rehabilitation is a viable treatment for clinically stable CVD patients [31]. Studies have shown telehealth-delivered exercise to be accessible and cost-effective in CVD patients [32, 33]. A possible means to reduce the financial impact associated with monitoring and rehabilitation of adults with chronic heart failure has been the judicious use of telehealth [34]: a recent study found potential to reduce costs associated with travel to attend medical appointments when replaced by telehealth delivery [35], and another study found equivalent care could be provided for lower cost [36]. The lack of larger, longer-duration high quality randomised controlled trials which redress lower rates of access and participation via innovative telerehabilitation and investigate the effect of exercise in adults with congenital heart pathologies prevents definitive exercise prescription as a treatment option for this cohort [37–39].

Biventricular congenital heart cohorts who undertake insufficient physical activity are at risk of impaired aerobic capacity and muscular strength, as well as potentially reduced neurocognitive function as documented in chronic heart failure populations, which may lead to further adverse outcomes and an increased burden on health systems. A strong justification is thus provided to investigate the effects of alternative modes of exercise prescription, such as structured telerehabilitation, to improve access to exercise training in people with congenital heart conditions. We hypothesise that, in this cohort, 16 weeks of a telehealth combined aerobic and resistance exercise training programme will demonstrate improvement in key physiological and psychological health parameters, compared with patients maintaining a usual and low level of activity.

## Methods

### Trial design

This will be a multi-site, two-armed, parallel-group, single-blind, superiority randomised controlled trial investigating the physiological and psychological effects of a telehealth-delivered 16-week aerobic and resistance exercise intervention in a biventricular congenital heart cohort, employing pre- and post-intervention measurements, with an 8-month follow-up.

### Trial setting and sites

Recruitment will occur at the Royal Prince Alfred Hospital, Royal Melbourne Hospital, Prince Charles Hospital, and Fiona Stanley Hospital in Australia. Potential recruits will be identified from the National Congenital Heart Disease Registry and trial site cardiologists. We include multiple sites in order to enhance participant enrolment and reach our target sample size.

### Participants

Medical records and telephone screening will be used to determine if potential recruits fulfil trial eligibility criteria. Treating or study physicians will confirm the suitability of potential recruits to enrol in the trial. Trial team members have consulted with various consumer organisations comprising individuals and their families with lived experience of congenital heart conditions while designing the trial, and this is expected to positively affect participant recruitment numbers. Additionally, information about the trial as well as participant information and recruitment material will be placed on institutional and study partner social media platforms and websites. A dedicated website page (https://www.hri.org.au/ch-fit-online-registrations) has been created where individuals can register their interest to participate and who can then be triaged to their nearest trial site.

### Inclusion criteria

Patients 16–55 years with biventricular congenital heart conditions of varying complexity, physiological stage B-C according to International Guidelines [40], and medically stable, who are > 6 months post-cardiac surgery as identified at the listed participating sites, and who may also present with conditions such as repaired tetralogy of Fallot and transposition of the great arteries, will be included. We have kept our inclusion criteria broad in order to achieve adequate participant enrolment.

### Exclusion criteria

Exclusion is (1) based on the last cardiologist’s assessment present in the recruit’s medical record and (2) determined at pre-intervention exercise testing. Exclusion criteria include simple lesion without sequelae such as a small ventricular septal defect, severe active enlargement of aorta, poorly controlled arrhythmias/blood pressure prior to or during exercise, non-optimal medical therapy and clinically unstable conditions in the preceding 3 months, severe outflow tract obstruction, severe valvular regurgitation, and uncontrolled systemic hypertension or decompensated heart failure (New York Heart Association (NYHA) class IV).

Further exclusion criteria include a physiological stage of D (severe hypoxaemia, systemic level pulmonary hypertension, Eisenmenger syndrome, refractory end-organ dysfunction) [40] as well as intellectual and/or physical disability preventing self-directed exercise, pregnancy or planned pregnancy (within 12 months), planned surgical intervention (within 2 years), self-reported volumes of PA or exercise sufficient to meet current minimum PA and exercise guidelines, and/or with no or an unreliable Internet connection. Our exclusion criteria aim to minimise the possibility of adverse or serious adverse events occurring, while still allowing for a broad recruitment strategy.

### Participant consent and withdrawal

Written, informed consent will be obtained at baseline visits, prior to assessment and randomisation, by site staff. Should an enrolled participant withdraw during the trial, they will be requested to complete a withdrawal form. Data collected from these participants will be retained for intention-to-treat analysis where consent is provided to retain data. Additional written, informed consent pertaining to outcomes requiring the collection of biological specimens via venesection and/or cannulation will also be obtained.

### Power analysis and statistical measures

A sample size of 100 is predicted to have ≥ 90% power (two-sided *α*: 5%) in estimating a VO_2peak_ difference of 10% between intervention and control (primary outcome), as suggested by preliminary findings [41]. We assume a 10% drop-out for a 16-week duration. Generalised linear mixed models with random subject and site effects (to control for variation between individuals and the clustering effects of site) and group-time interactions will be used to estimate the between and within group pre- and post-intervention changes in the primary outcome, controlling for covariates that may influence the outcome. Results will be summarised using descriptive and inferential statistics, with relevant *P* values (significance < 0.05). Sensitivity analysis of per-protocol vs intention-to-treat will be conducted. We will handle missing data by imputation using the closest match method. i.e. substitute a same time-point value from a participant with the closest value for the measured variable at other time points [42].

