### Randomisation and concealment

Computer-generated randomisation will be stratified on a 1:1 allocation by site, baseline aerobic exercise capacity (% predicted VO_2peak_), physiological stage (B or C), age, and sex (female, male), per Fig. 1. An independent statistician/staff member will employ randomisation by minimisation to allocate participants. Where possible, site assessors will be blinded to participant group allocation and identification. Participants’ data and identification will be stored centrally (REDCap™) and accessible only by a trial coordinator (uninvolved in participant enrolment, randomisation, or assessment). Unblinding is expected to occur in the event of a serious adverse or adverse event. Participants are not blinded owing to the nature of the intervention (exercise).

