## Discussion

We have developed a protocol for an adequately powered, multi-centre, 16-week randomised controlled trial with an 8-month follow-up period investigating the effects of telerehabilitation in adults (≤ 55 years) and adolescents (≥ 16 years) diagnosed with biventricular congenital heart conditions. To the best of our knowledge, this will be the first trial delivering such an intervention via a novel platform (telehealth) to this cohort. We have adopted a pragmatic approach in our inclusion and exclusion criteria to enhance recruitment, while simultaneously limiting the potential for adverse events to occur in a group with cardiac physiologies of varying complexity.

A strength of our protocol is the objective measurement of key physiological variables during exercise training as well as objective confirmation of compliance and adherence to the exercise intervention. The monitors used during exercise provide real-time data, and detailed feedback is available from the Polar Flow Mobile App™. In addition, our trial intervention and objectives have been developed in consultation with consumer organisations such as HeartKids and the Australian and New Zealand Fontan Registry, comprising individuals and their families with lived experience of congenital heart conditions as well as people with significant expertise in the management and support of those affected by congenital heart conditions. This is expected to assist in recruitment as well as maintaining trial compliance and adherence.

A possible limitation of our study could be the multi-centre facet, which has the potential to introduce discrepancies in accuracy and reliability of collected data and measurements of physiological and psychological parameters. We address this limitation in two ways: (1) we use self-administered and validated online tests, which reduces both assessor bias and non-reproducibility of results, and (2) we have developed standard quality assurance and control procedures for use of required equipment in line with manufacturer’s specifications. All staff will have received standardised training prior to interacting with participants. We are thus able to leverage a robust geographical diversity.

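### Read as a site intercept, the random site effect cancels from the group-by-time contrast, so it does not control site clustering in the primary 16-week comparison (minor; slightly conservative test)

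*Protocol article*

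**What the plan says.** The section on power analysis and statistical measures specifies "Generalised linear mixed models with random subject and site effects (to control for variation between individuals and the clustering effects of site"). The same sentence says that "group-time interactions will be used to estimate the between and within group pre- and post-intervention changes in the primary outcome", and adds "controlling for covariates that may influence the outcome" without naming the covariates. Group by time is the only interaction with time that is named. The text does not say whether the site effect is an intercept only.

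Under Randomisation and concealment, "Computer-generated randomisation will be stratified on a 1:1 allocation by site" and four further factors, carried out by minimisation. Table 2 plans four sites with near-equal arms in each (intervention/control): 17/18, 13/12, 8/7 and 12/13.

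The Discussion states: "A possible limitation of our study could be the multi-centre facet, which has the potential to introduce discrepancies in accuracy and reliability" of the collected data. It answers this with validated self-administered tests, equipment quality procedures and standardised staff training.

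**The concern.** The site term is given a job, controlling the clustering effects of site, and the primary effect is a difference between arms in within-participant change. A site intercept acts on the level of VO2peak and not on its change, so on the usual reading the term cannot do that job for this contrast. Sites may still differ in mean change over 16 weeks. Because the trial balances allocation by site, an analysis that leaves such shared differences in the residual gives up some of the precision that the balancing was meant to secure. At stake are a modest loss of power and a methods statement that claims more than the model delivers.

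**Working it through.** **Inputs from the protocol article.** Four sites with the Table 2 arm sizes, 50 per arm; two-sided 5% test; target difference 10%; "A sample size of 100 is predicted to have ≥ 90% power"; 10% dropout over 16 weeks. **Assumed, because the documents do not give them:** the SD of change within site (σ) and the between-site SD of mean change (τ), both in percentage points on the scale of the 10% target.

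**1. The plan's own power figure.** It cannot be reproduced without an SD. Solving backwards, 90% power needs σ of at most 14.6 with 45 completers per arm, or at most 15.4 with 50 per arm. Check for 45 per arm: SE = 14.6 × √(2/45) = 3.08; 10/3.08 = 3.25; 3.25 − 1.96 = 1.29, which is about 90%. Since 45/0.9 = 50 per arm, N = 100 is coherent for σ near 14.6. I use σ = 15 with 100 completers below.

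**2. Cancellation.** Write the outcome of participant i at site s and visit t as

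y = (fixed part, including group × time) + u_s + b_i + e_it.

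The change from baseline is y_i1 − y_i0 = (fixed change) + (e_i1 − e_i0). Both u_s and b_i have gone. With complete data the interaction SE is √[2σ_e² × (1/50 + 1/50)], with no site variance in it.

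- σ_e² = 6.25: √(12.5 × 0.04) = 0.7071. Generalised least squares with the Table 2 sizes gives 0.7071 for site variance 0, 16 and 400.
- σ_e² = 106.6: √(213.2 × 0.04) = 2.920. Generalised least squares gives 2.92027 for site variance 0, 25, 100 and 400, with two or three visits.
- With 10 dropouts and two visits, the SE moves only from 3.0560 to 3.0566 as the site variance goes from 0 to 400.
- Mixed models fitted with and without the site intercept gave the same estimate to rounding error, and SEs that agree to within 0.0001.

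**3. What remains in the residual.** Let sites differ in mean change with SD τ, equally in both arms. The site shares are 0.35, 0.25, 0.15 and 0.25, and their squares sum to 0.1225 + 0.0625 + 0.0225 + 0.0625 = 0.27. Without a site-by-visit term, the expected residual variance of change is about σ² + τ² × (1 − 0.27) × 100/98 = 225 + 0.745τ². The SE ratio is the square root of this over 225:

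- τ = 3: √(231.7/225) = 1.015
- τ = 5: √(243.6/225) = 1.041
- τ = 8: √(272.7/225) = 1.101

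With site-by-visit the SE is about 15 × √(2/50) = 3.00 whatever τ is.

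**4. Simulation** (40,000 trials per row; Table 2 sizes, σ = 15, true difference 10 for power and 0 for type I error; change-score equivalent of the model):

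| τ | SE without / with site-by-visit | Inflation | Type I error without / with | Power without / with |
|---|---|---|---|---|
| 0 | 2.99 / 2.99 | 0% | 4.8% / 4.7% | 91.0% / 90.9% |
| 3 | 3.04 / 3.00 | about 1% | 4.7% / 5.0% | 90.4% / 90.8% |
| 5 | 3.11 / 3.00 | about 4% | 4.4% / 5.1% | 89.8% / 91.1% |
| 8 | 3.29 / 2.99 | about 10% | 3.4% / 5.1% | 86.9% / 90.9% |

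The mean estimate under no effect was zero to within simulation error in every row, so there is no bias.

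**The case against.** The strongest reply is that the text does not fix the site effect as an intercept. Random site effects could include a site-by-time term, the unnamed covariates could include site, and an article may leave such detail to the analysis plan. This stands as a limit on certainty. But the sentence names a model and states what it achieves. On the ordinary reading that statement is wrong for the primary contrast, and no site-by-time term is mentioned.

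The second reply is size. Nothing is lost if sites do not differ in change, and little at modest differences. A between-site SD of 8 points would be large beside a 10-point target effect, and nothing in the documents supports it. This also stands, and it is why the point is minor.

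Four stronger readings are tempting, and the documents do not support them:

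- *The SE is too large whenever sites differ.* This holds only for differences in change that both arms share. If the treatment effect itself varies by site, the SE is too small for inference beyond these four sites. With σ = 14.6, it is 2.94 against a true 3.27 when the between-site SD of the effect is 0.2 of σ, and 3.06 against 4.75 at 0.5. Type I error is then 7.5% and 20%. Neither a site intercept nor site-by-visit alone corrects that.
- *The Discussion admits site drift.* It speaks of accuracy and reliability across centres and does not mention change over time. A stable calibration offset at a site cancels from each participant's change and does no harm here, and the same paragraph describes mitigation.
- *A variance estimated from only four sites will often come out as zero.* That may be so, but if the intercept cancels, its estimate has no consequence for the primary result.
- *The trial risks a false positive through this mechanism.* With shared site differences the error is in the conservative direction.

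**Conclusion.** The point holds in a limited form. If the random site effect is an intercept, it contributes nothing to the primary change comparison, and the stated control of clustering is not delivered there. The cancellation is algebra and needs no assumed values beyond the intercept reading. The cost does rest on assumptions: σ of 15 points, 100 completers, and site differences in change common to both arms. On those, the SE is inflated by 0% to about 10% as τ runs from 0 to 8 points, and power falls below 90% only from about τ = 5. The estimate stays unbiased. Severity is minor: a matter of precision and accurate description, not of validity.

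**What to change.** In the power analysis and statistical measures section, add site (four levels) by visit as fixed effects to the primary model and keep the random participant effect. If the site effect was already meant to vary with visit, say so. Limit the sentence on site clustering to what the model does: it removes site differences in level and in mean change that are shared by both arms. It does not address variation of the treatment effect between sites.

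The cost is one line of specification and three degrees of freedom per visit, negligible with about 100 participants: at τ = 0 the SE is 2.99 either way. The gain is an SE that no longer depends on shared site differences, in an analysis that respects a factor already used in allocation.
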